## Abstract

**Background:**

Alcohol and other drug use and misuse is a significant problem amongst Polish youth. The SFP10-14 is a family-based prevention intervention that has positive results in US trials, but questions remain about the generalizability of these results to other countries and settings.

**Methods/Design:**

A cluster randomized controlled trial in community settings across Poland. Communities will be randomized to a SFP10-14 trial arm or to a control arm. Recruitment and consent of families, and delivery of the SFP10-14, will be undertaken by community workers. The primary outcomes are alcohol and other drug use and misuse. Secondary (or intermediate) outcomes include parenting practices, parent–child relations, and child problem behaviour. Interview-based questionnaires will be administered at baseline, 12 and 24 months.

**Discussion:**

The trial will provide information about the effectiveness of the SFP10-14 in Poland.

**Trial registration:**

International Standard Randomised Controlled Trial Number: ISRCTN89673828

## Background

The European Union (EU) is the heaviest drinking region of the world, drinking 11 litres of pure alcohol per adult each year [1]. More than 1 in 4 deaths among men (aged 15–29 years) and 1 in every 10 deaths among young women in the EU is alcohol related [2]. Young people (aged 15–24 years) are responsible for a high proportion of this burden, with over 25% of youth male mortality and approximately 10% of young female mortality being due to alcohol [1]. Sparse information exists on the extent of social harm in young people, despite the fact that a third of a million (6%) 15–16 year old school students in the EU report engaging in fights, and 200,000 (4%) report unprotected sex, due to their own drinking [1].

Alcohol and other drug use increases markedly between the ages of 11 and 15 years amongst young people in Poland. Between the ages of 11 and 15 the proportion of those who have ever smoked increases from 12% to 59%. At age 11, 10% of 11-year-olds report that they have ever been drunk, and this increases to 53% amongst 15-year-olds. Moreover, 18% of Polish youth report lifetime cannabis use [3]. Early alcohol and other drug use is associated with a range of subsequent adverse health and social outcomes [4-11].

The Strengthening Families Program 10–14 (SFP10-14) is a US-developed family-based intervention for preventing alcohol and other drug use and problems amongst young people. It has been evaluated in two large-scale randomized controlled trials in Iowa, USA [12-16] and has informed the development of a family-based intervention for African American families evaluated in a large randomized controlled trial in rural Georgia, USA [17-19]. Several systematic reviews have highlighted the promising results from these trials but also note the question of whether this US-developed intervention will be applicable in other countries and settings [20-25].

### Aims of the project

The aim of the trial is to assess the effectiveness of the Polish version of the SFP10-14 (“Program Wzmacniania Rodziny”) when compared with a control group, in a large randomized controlled trial in Poland.

The objectives of this trial are:

· To examine the effectiveness of the SFP10-14 in promoting positive parenting practices in parents of 10–14 year-olds in Poland

· To examine the effectiveness of the SFP10-14 in promoting positive parent–child relations amongst families with 10–14 year-olds in Poland

· To examine the effectiveness of the SFP10-14 in reducing problem behaviour amongst 10–14 year-olds in Poland

· To examine the effectiveness of the SFP10-14 in preventing alcohol and drug use and misuse amongst 10–14 years-olds in Poland

## Methods/Design

### Design

A parallel group cluster randomized controlled trial where communities will be randomly assigned, with concealed allocation, to one of two groups, with a 1:1 allocation ratio. Communities in the intervention arm will participate in SFP10-14 group sessions; communities in the control arm of the trial will receive information leaflets for families. All families recruited into the trial will be assessed at baseline and at 12 and 24 months follow-up. Two years after baseline data collection, families from control communities will be offered the opportunity to participate in SFP10-14.

### Ethics

Research undertaken in Poland funded by the National Bureau for Drug Prevention is reviewed by independent experts, and this independent review process covers scientific and any ethical issues that are identified by the independent reviewers. Ethics Committee approval for data collection was obtained from “Komisji Bioetycznej przy Instytut Psychiatrii I Neurologii W Warszawa” (Ethics Committee of the Warsaw Institute for Psychiatry and Neurology). Each family recruited into the trial receives an information sheet describing the trial and data collection procedures before giving their written and signed consent to participate. Consent was obtained from parent(s) and, separately, from children.

### Setting and participants

Eligible participants are families with 10–14 year-old children from community settings across Poland. In all families at least one parent should agree to participate. If two children from the same family are involved in the intervention group then both parents will be asked to participate in SFP10-14 group sessions.

### Recruitment

Communities who have expressed an interest in the SFP10-14 will be approached in 2010 to participate in the trial. Information about the SFP10-14 has been disseminated throughout Poland via conferences, journal articles, information bulletins and personal contact. Within communities, families will be recruited by community workers. Family recruitment will take place through community agencies, schools and via information leaflets and personal contact.

### Randomization

Randomization occurs after communities have consented to participate in the trial. Simple randomization of community to intervention or control arm will be undertaken by the lead investigator drawing names out of a hat in a concealed allocation format.

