### Blinding

Due to the nature of the intervention blinding of participants, SFP10-14 facilitators and data collectors is not possible.

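### Nothing requires families to be consented and interviewed before their community's arm is known, so concealment covers only the community draw and the arms can enrol different kinds of families

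*Protocol article*

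**What the plan says.** All references are to the protocol article.

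- **Unit and concealment.** Under Design, "communities will be randomly assigned, with concealed allocation, to one of two groups, with a 1:1 allocation ratio". Under Randomization, the draw is "undertaken by the lead investigator drawing names out of a hat in a concealed allocation format".
- **Timing.** The only timing statement is in Randomization: "Randomization occurs after communities have consented to participate in the trial". It does not mention family consent or the baseline interview.
- **Who recruits.** The Abstract (Methods/Design) states: "Recruitment and consent of families, and delivery of the SFP10-14, will be undertaken by community workers". The Recruitment section agrees: "Within communities, families will be recruited by community workers". The routes are open to discretion: "Family recruitment will take place through community agencies, schools and via information leaflets and personal contact".
- **Blinding.** The Blinding section says that "blinding of participants, SFP10-14 facilitators and data collectors is not possible".
- **Data collection.** Interviews take place at baseline, 12 and 24 months. The same section sets a rule, for the control group only, on which parent and which child complete the questionnaire, and does not exempt baseline from it.
- **What each arm offers.** The intervention is seven weekly sessions of two to three hours (Intervention). Control communities receive leaflets, and their families are offered the programme two years after baseline (Design).
- **Analysis.** Analyses are multilevel and by intent to treat, with complete-case and multiple-imputation versions. No adjustment for baseline differences is named.

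**The concern.** In a cluster trial, concealing the draw of clusters guards against choosing which community goes to which arm. It does not guard the later step at which families are approached and agree. If the arm is known by then, workers may approach different families, and different families may accept.

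The two offers are far apart in what they ask of a family now: seven weekly sessions in one arm, leaflets in the other. Time, motivation and perceived family difficulty could all influence who agrees. The Analyses section itself treats family problems and child behaviour severity as subgroup factors on the strength of pilot results, so the investigators regard these traits as relevant to outcome or to response.

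At stake is the main comparison on alcohol and drug use. A difference at 24 months could reflect who was enrolled rather than what the programme did, in either direction. Agency referral of troubled families to the programme would hide a benefit; self-selection of motivated families would mimic one.

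**Working it through.** **Step 1: what the text permits.** Set the sections side by side.

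1. Randomization gives an earliest point for the draw (after community consent) and no latest point relative to family enrolment. A team that drew arms on the day the community consented, and only then began recruiting families, would comply fully.
2. The Abstract mentions randomization of communities first and recruitment of families next. The body puts Recruitment before Randomization. Neither order is a timeline, so layout does not settle the matter.
3. The control-only rule in Data collection can be applied at the baseline interview only if the arm is known by then. This is the strongest internal sign that baseline follows allocation. It concerns questionnaires, so it does not by itself date consent.
4. Recruitment, consent and delivery fall to one class of worker. No independent recruiter, or recruiter unaware of the arm, is described.

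The text therefore permits enrolment with the arm known, points towards it, and contains no safeguard against it.

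**Step 2: why the planned analysis does not remove it.** Let *s1* and *s0* be the shares of high-risk families enrolled in the two arms, and *pH* and *pL* the outcome risks in high-risk and low-risk families. With no intervention effect, the expected outcome in arm *a* is pL + s_a × (pH − pL), so

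spurious difference = (s1 − s0) × (pH − pL).

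The number of families does not appear, so a larger sample does not reduce it. Intent to treat keeps enrolled families in their arm, but the selection happens before enrolment. Multilevel modelling corrects the standard error for clustering and does not restore the balance of families.

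**Step 3: illustration only.** The document gives neither the difference in mix nor the difference in risk, so both are assumed:

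- 0.10 × 0.20 = 2 points
- 0.20 × 0.20 = 4 points

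The effect on the false-positive rate was computed for a two-sided 5% test of two proportions (normal approximation, unpooled standard error). Of the inputs, only the total of 600 families is in the document. An equal split to 300 per arm, 30% high-risk families in one arm, low-risk outcome risk 20%, high-risk outcome risk 40% or 60%, and design effects of 1, 1.5 and 2.45 are all assumed.

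One case in full: 10 points more high-risk families, high-risk outcome risk 60%, design effect 1.

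- Arm risks: 0.20 + 0.40 × 0.30 = 0.32 and 0.20 + 0.40 × 0.40 = 0.36
- Standard error: √[(0.32 × 0.68 + 0.36 × 0.64) / 300] = 0.0386
- Standardised shift: 0.04 / 0.0386 = 1.035
- Rejection rate: 1 − Φ(1.96 − 1.035) + Φ(−1.96 − 1.035) = 17.9%

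| Excess of high-risk families | Spurious difference | Rejection rate, no true effect |
|---|---|---|
| 0 points | 0 | 5.0% |
| 5 points | 1 to 2 points | 5.4% to 8.2% |
| 10 points | 2 to 4 points | 6.4% to 17.9% |
| 20 points | 4 to 8 points | 10.7% to 53.5% |

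The ranges run over the two high-risk outcome risks and the three design effects. The table shows how the mechanism scales. It does not estimate what happened in this trial.

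**The case against.** The strongest reply is that the order is inferred. No sentence says that families are recruited after randomization, and a condensed article may leave the sequence to the full protocol. Several stronger readings are tempting, and the document does not support them:

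- **That families were definitely enrolled after allocation.** The timing statement allows the reverse order too. The control-only questionnaire rule suggests the arm is known at the baseline interview, but consent could still have come earlier.
- **That the same individuals recruit and deliver.** The Abstract gives both tasks to community workers as a class, and the Intervention section speaks of trained facilitators. The overlap is of role, not demonstrably of person. The Blinding section does not name recruiters either.
- **That the arms will differ, are no longer comparable, or lack a true pre-allocation baseline.** Each depends on the order of events, and nothing shows that an imbalance arose.
- **That 2 to 4 points is an estimate of the bias.** It is the product of two assumed figures.

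There is also mitigating text. The Design section offers control families the programme later, which narrows the gap between the two offers. The Ethics section has every family receive an information sheet before signed consent, though it does not say whether the sheet is the same in both arms.

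These limits stand, and they restrict the point to what the plan permits. They do not dispose of it. The article chose to state when the draw happens, what is concealed and who recruits, and a trial that follows those statements exactly is open to this bias. A programme deferred by two years is not the same offer as one starting now, so the later offer may reduce the difference without removing it.

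**Conclusion.** The point holds as a weakness of the stated design: randomization is tied to community consent alone, and nothing protects the enrolment and first interview of families from knowledge of the arm. That the arm is known at enrolment is the natural reading, not an explicit statement. If it is right, concealment covers only the community draw, and the arms can enrol different kinds of families. Neither intent-to-treat nor multilevel analysis would remove the resulting bias.

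The size cannot be derived from the document. The 2 to 4 points and the rejection rates rest wholly on assumed differences in family mix and risk, and should be read only as showing that modest imbalances matter. If families were in fact consented and interviewed before allocation was disclosed, one sentence saying so would close most of the concern, and the control-only questionnaire rule would need to be squared with that order.

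**What to change.** **Main change.** Amend the Randomization section so that, in each community, families are identified, consented with the same information sheet for both arms, and given the baseline interview before that community's allocation is drawn or disclosed. The sheet can describe both possibilities already in the Design section: the programme now, or the offer of it after two years. The rule on who completes the baseline questionnaire must then be the same for all families, because no control group is yet known at that point.

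*Cost.* The steps are already planned and only their order changes. Allocation is delayed, by a length that cannot be judged here because the article gives neither the number of communities nor the pace of recruitment. Some families who consent before allocation may not attend the sessions; they stay in the intent-to-treat analysis, which dilutes the estimated effect somewhat.

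**Where families were already recruited after allocation.** The Ethics section refers to consent in the past tense, so this may apply to some communities. In that case:

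- adjust the primary analysis in the Analyses section for the baseline outcome, child age and the family-risk variables already collected;
- report families approached and consenting by arm, where these were recorded;
- state that adjustment repairs the bias only in part. It cannot reach unmeasured traits such as motivation, and baseline answers given with the arm known may themselves be affected.

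*Cost.* No new data collection for the adjustment; the flow figures depend on what community workers recorded.

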### Sample size calculation

No formal sample size calculation was undertaken but funding was requested for a sample size (N = 600 families) which was similar to that reported in other trials of the SFP10-14 [12-16]. These other trials have reported SFP10-14 effectiveness for reducing a number of risky behaviours amongst young people, including alcohol and drug use and misuse and other behavioural problems.

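### Simple randomization of communities from a hat does not clearly secure the 1:1 ratio and does nothing to balance community characteristics

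*Protocol article*

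**What the plan says.** The unit of randomization is the community. The Design section describes "A parallel group cluster randomized controlled trial where communities will be randomly assigned, with concealed allocation", and the assignment is "to one of two groups, with a 1:1 allocation ratio".

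The Randomization section gives the timing, "Randomization occurs after communities have consented to participate in the trial", and then the method: "Simple randomization of community to intervention or control arm will be undertaken by the lead investigator drawing names out of a hat". It adds that this is done in a concealed format. It mentions no blocking, stratification, matching or minimization, and does not say whether the draw stops at half the names.

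The Sample size calculation section gives a target of 600 families and no number of communities. The Analyses section accounts for clustering at community and family level by multi-level analysis and names no community-level covariates for adjustment.

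**The concern.** The article fixes the method, the device and the person making the draw, so this is a stated design choice and not a detail left to a fuller document.

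Two separate issues arise.

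- **Arm sizes.** In its usual sense, simple randomization assigns each unit independently and gives 1:1 only on average. With few units, the realised split can be well away from equal.
- **Balance of characteristics.** The communities come from across Poland and are approached because they expressed interest in the programme. They may differ in size, setting and baseline level of substance use. Imbalance in such a trait affects whole clusters at once, and recruiting more families within the same communities does not remove it. Communities consent before the draw, so their characteristics are available for balancing but are not used.

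At stake are the precision of the effect estimate and how readily a reader will accept an observed difference as due to the programme. Credibility of the allocation carries extra weight because the Blinding section says that participants, facilitators and data collectors cannot be blinded.

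**Working it through.** The plan gives no calculation on this point, so there is no figure to reproduce. The stated 1:1 ratio is checked against two readings of the Randomization section.

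**Inputs.** From the article: two arms, 1:1, communities as units, 600 families, groups of up to 15 families (Intervention section). Assumed: the number of communities, K, taken as 20, 40 or 60, which is 30, 15 or 10 families per community.

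The order of magnitude can be checked. With 1:1 allocation of families there are 600 / 2 = 300 in the intervention arm, and 300 / 15 = 20 full groups. At one full group per community, K = 2 × 20 = 40. Several groups per community would mean fewer communities, smaller groups would mean more. This makes the range plausible but does not fix K.

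**Reading A: each community assigned independently with probability one half.** The number in one arm is X ~ Binomial(K, 0.5).

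- P(exactly equal) = C(K, K/2) / 2^K
- P(60:40 or worse) = P(X ≤ 0.4K) + P(X ≥ 0.6K)

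| K | Exactly equal | 60:40 or worse | 2:1 or worse |
|---|---|---|---|
| 20 | 17.6% | 50.3% | 11.5% |
| 40 | 12.5% | 26.8% | 3.8% |
| 60 | 10.3% | 15.5% | 1.3% |

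The efficiency of a split s:(1−s) relative to equal arms, with communities of equal size, is 4s(1−s):

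- 60:40: 4 × 0.6 × 0.4 = 0.96, a loss of 4%
- 2:1: 4 × (2/3) × (1/3) = 0.89, a loss of 11%

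Unequal arms alone are therefore a modest cost.

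**Reading B: half the names drawn without replacement.** For even K the split is exactly K/2 to K/2, and the 1:1 ratio is met. Take a trait held by half the communities and let x be the number of intervention communities that have it. Then x is hypergeometric:

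- P(x) = C(K/2, x)² / C(K, K/2)
- difference in proportions = |2x − K/2| / (K/2)

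For K = 20 the difference moves in steps of 20 points, so a difference of 20 points or more means any imbalance at all:

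1 − C(10, 5)² / C(20, 10) = 1 − 63,504 / 184,756 = 0.656.

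| K | Trait differs by 20 points or more | SD of standardized difference, 2/√K |
|---|---|---|
| 20 | 65.6% | 0.45 |
| 40 | 34.3% | 0.32 |
| 60 | 19.6% | 0.26 |

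The last column applies to any single community-level covariate. Equal arms do not cure trait imbalance; stratification, matching or constrained randomization is needed for that.

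**The case against.** The strongest defence is that drawing names from a hat is naturally read as drawing without replacement from one pool. If half are drawn, the split is exactly 1:1 and the binomial figures do not apply. "Simple" may only mean unstratified, and 1:1 may mean the intended ratio. This stands as far as it goes: no contradiction between the Design and Randomization sections is established, only an ambiguity. It does not touch the balance of characteristics, which is absent under both readings.

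Second, simple randomization is legitimate, and a correct multi-level analysis reflects chance imbalance in its standard errors. This also stands, and it limits the harm to lost precision and weaker credibility.

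Third, the size depends on a number that the article does not give, and it falls clearly as K rises. That is why a range is shown. The article does not itself say that the communities are few.

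A reader might infer two stronger points that the document does not support.

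- **That the draw cannot be audited.** The article is silent on a witness or log. A hat draw can be witnessed and recorded, and a journal article commonly leaves such details to the full protocol.
- **That a draw by the lead investigator biases the allocation.** Allocation is stated to be concealed and follows community consent, and a genuine draw cannot be predicted by the person making it. No route to selection by that person is shown. What remains is appearance: an interested party makes the draw and no independent person is named.

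**Conclusion.** The point holds as a weakness in a stated design choice. The method as worded does not clearly secure the 1:1 ratio, and under either reading it leaves community characteristics to chance although they could be known before allocation.

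Trait imbalance is the main harm. With 20 to 60 communities, it reaches 20 points or more with probability from about 66% down to about 20%, for a trait held by half of them and with equal arms. Unequal arm sizes matter less: a 60:40 or worse split has probability from about 50% down to about 15.5% if assignment is independent, but a 60:40 split costs only 4% in efficiency.

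These figures rest on the assumed number of communities. The efficiency figures also assume communities of equal size. The randomization itself remains valid.

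**What to change.** Replace the hat draw with computer-generated restricted randomization of the consented communities, with equal numbers per arm. Stratify, match or constrain on a few characteristics known before allocation; size and urban/rural setting are examples, since the article does not name prognostic community factors. Store the seed and have the allocation generated by an existing team member who is not involved in recruitment. Include the balancing factors in the multi-level model. State the planned number of communities in the protocol.

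If the draw has already taken place, report how many communities were in the pool, whether exactly half were drawn, and who drew, witnessed and recorded it. Specify adjustment for key community characteristics before outcome data are examined.

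The cost is a short script and some protocol wording. The real downside is that communities must be allocated in one or more batches, so those that consent early may wait.
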